### Primary outcome

The primary outcome of this study is walking capacity which will be assessed using the Self-Paced Walking Test (SPWT). The SPWT represents the current gold standard for assessing walking capacity in patients with LSS [9, 25]. During this test, participants will be asked to walk freely on a leveled surface at their own pace until they are forced to stop for a minimum of 3 s because of LSS symptoms. The time and distance reached by the participants will be measured. The minimal clinically important change (MCID) reported for the SPWT varies between 319 and 376 m [26]. As patients with LSS causing NC are at higher risk of falls, participants will walk near a ramp and a research assistant will also walk behind the participant during the walking test to assist if needed.

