### Adverse events and harms

All adverse events (minor or major) associated with both intervention and usual care will be monitored using open-ended questions. Adverse events are defined as any undesirable experience occurring to a participant, with or without relation to the intervention. These undesirable experiences include an increase in back or leg pain intensity and claudication discomfort. Each adverse event reported by participants throughout the study will be considered and discussed with the research team. Adverse events that are associated with an increase in disability will be reported to the ethics committees. There is no anticipated harm and compensation for trial participation.

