Regarding rehabilitation programs, the effectiveness of exercises alone in improving objective walking capacity is still not well established [17]. A recent systematic review reported low to moderate-quality evidence for multimodal programs including exercises on the improvement of symptoms and function in patients with LSS causing NC [45]. In addition, another previous RCT showed that the use of supervised exercises provided significantly greater improvement in walking distance, physical function, and symptoms severity compared to self-directed exercises [46]. Similarly, another RCT of Comer et al. showed that a self-directed home exercise program including flexion and aerobic exercises punctually prescribed by physiotherapists did not systematically improve symptom severity and was no more effective than education and advice [22]. However, in most previous RCTs, exercise intensity was not tailored to day-to-day symptom severity. Thus, the present protocol is innovative in two respects: it includes standardized education for all participants, and it takes into consideration the day-to-day evolution of symptom severity to provide a tailored exercise program.

Previously reported rehabilitation programs usually included aerobic and lower limb-strengthening exercises [20, 47–50] but did not incorporate balance-strengthening exercises. However, patients with LSS and NC present an increased risk of falls for a variety of reasons, including deconditioning, lower extremity neurological deficits, polypharmacy, environmental hazards, poor vision, and impairments in gait and activities of daily living [51]. In addition, a previous study by Thornes et al. showed that there was a large inter-individual variation in balance between patients with LSS and NC and that gait stability was negatively associated with disability as measured by the ODI [52]. Based on those findings and knowing that balance limitations have been identified in 45 to 65% of patients with LSS [53, 54], the present protocol will include balance exercises to help decrease the risk of falls in patients with LSS causing NC and to contribute to patient’s self-confidence during walking.

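### After baseline, falls are recorded only through open-ended adverse-event questions, which may capture them more fully in the exercise arm; one falls count at the four shared visits would equalise the opportunity to report

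*Protocol article*

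**What the plan says.** Under Adverse events and harms, the protocol article states that all adverse events, minor or major, "will be monitored using open-ended questions". It does not say when the questions are put or by whom. The definition is wide and does not depend on a link to the intervention. The examples concern symptoms: "These undesirable experiences include an increase in back or leg pain intensity and claudication discomfort". On scope: "Each adverse event reported by participants throughout the study will be considered and discussed with the research team". The section ends: "There is no anticipated harm and compensation for trial participation".

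Fall risk is acknowledged elsewhere. Under Primary outcome: "As patients with LSS causing NC are at higher risk of falls, participants will walk near a ramp". The second precaution named there is an assistant who follows close by in case help is required. The Discussion reports that "balance limitations have been identified in 45 to 65% of patients with LSS" and that "the present protocol will include balance exercises to help decrease the risk of falls in patients with LSS causing NC".

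Under Data collection, the number of falls in the preceding 6 months is part of the baseline questionnaires. Table 1 lists no falls item at any later visit. Leg and back pain are rated on a numerical rating scale (NRS) at all five visits.

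**The concern.** Falls are a harm that the protocol guards against in its own walking test and hopes to reduce through its exercises. Yet the baseline count has no stated counterpart at follow-up. Open-ended questioning depends on the participant thinking to mention an event and on how often someone is there to hear it. The arms differ greatly in the second respect: the exercise arm meets a kinesiologist three times a week for 6 weeks, while the control arm has only the shared assessments.

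What is at stake is the descriptive harms report. If session reports count, equal true fall rates could appear as more falls with exercise, or a true reduction could be masked. The report could not separate a difference in falls from a difference in reporting.

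**Working it through.** The plan states no figure on this point, so there is none to reproduce. The check is a count of planned occasions and a comparison of sections.

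**1. Fixed falls questions.** Baseline: one, in both arms (Data collection). Weeks 2, 4, 6 and 12: 0 of 4 visits (Table 1).

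**2. Planned contacts after baseline.** Inputs: three supervised sessions a week for 6 weeks, one at the outpatient clinic and two online (Intervention group); five assessments including baseline (Data collection); education given within the week 2 and week 4 assessments (Education), so it adds no contact in either arm.

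- Sessions, exercise arm: 3 × 6 = 18, of which 1 × 6 = 6 in person and 2 × 6 = 12 online. Control arm: 0.
- Shared assessments after baseline: 5 − 1 = 4 in each arm.
- Total: 18 + 4 = 22 against 0 + 4 = 4.
- In person only: 6 + 4 = 10 against 4.
- Up to and including week 6: 18 + 3 = 21 against 3.
- After week 6, up to week 12: 1 against 1. Any imbalance in opportunity therefore falls in the first 6 weeks.
- Adding one reminder call before each of the four assessments: 22 + 4 = 26 against 4 + 4 = 8. The gap of 18 is unchanged.

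These are opportunities to report. The ratio 22/4 = 5.5 is not an estimate of any ratio of recorded falls.

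**3. Does the contact gap become a reporting gap?** Only if events mentioned at training sessions enter the adverse-event record. The wording on scope takes in events reported at any time in the study and does not limit them to assessments. Data management says that a data sheet is completed at each intervention session but does not say that it records adverse events; the only session monitoring named under Interventions is attendance. If events are collected at the shared assessments alone and session reports are left out, the opportunities are 4 against 4 and this imbalance does not arise.

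**4. Size.** The document gives no fall rate and no reporting rate. Any figure for the distortion would come entirely from assumed values, so none is given.

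**5. Pain increase.** NRS for leg and back pain is scored at 5 of 5 visits in both arms. An increase in pain is therefore measured evenly, whatever the open-ended questions yield.

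**6. The harms sentence.** Set the closing sentence of Adverse events and harms beside the walking-test precautions. The precautions show that a fall during a trial procedure was foreseen. The tension is with the word *anticipated*.

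**7. With a fixed falls question.** Structured occasions after baseline become 4 against 4.

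**The case against.** The strongest reply has four parts.

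- **Falls are already covered.** The definition takes in any undesirable experience, and the symptoms named are examples. This stands. A reader might infer that falls are left out of adverse-event monitoring; the text does not support that.
- **There is no contradiction about harm.** Fall risk is described as a feature of these patients, adverse events are defined regardless of cause, and the exercises are supervised, adjusted to the patient's capacity and meant to lower fall risk. This largely stands. A reader might infer that the protocol concedes the exercises are hazardous and then denies it. The document says no such thing, and precautions can coexist with an expectation that no harm will follow. What remains is loose wording.
- **The article may leave the timing and form of the questions to the full protocol.** This is fair as regards the missing detail, and unequal capture is accordingly a risk and not an established fact. But the article does fix an itemised visit schedule that omits falls, a falls count at baseline, and an open-ended method with a scope covering the whole study. A change to that stated method can be judged on its merits.
- **The consequence is small.** No between-arm test of falls is planned, falls are not an outcome, and 12 of the 18 extra contacts are remote. All true. A reader might still infer that the trial will report a biased fall comparison; that would require session reports to be counted and a comparison to be drawn from them, and neither is stated.

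**Conclusion.** The point holds as a cheap improvement to how falls are ascertained. After baseline the protocol has no fixed falls question, relies on open-ended reporting with no stated occasion, and gives one arm 18 more contacts at which a fall could be mentioned (22 against 4). Whether this makes recording unequal depends on one assumption, that reports made at sessions are counted. The scope wording allows this but does not require it. The amount cannot be determined from the document.

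The harms sentence is a secondary matter of wording. The primary and secondary analyses, alpha, power and sample size are untouched.

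**What to change.** 1. At weeks 2, 4, 6 and 12, ask both arms for the number of falls since the last visit. Ask for the number only, not where the fall happened, so that the answer does not reveal the allocation to the blinded assessor.
2. Base the descriptive between-arm report of falls on that item alone, without a test.
3. Add a falls field to the training-session sheet and list those falls separately, so that no safety information is lost.
4. In Adverse events and harms, name falls among the examples, and replace the statement on harm with one saying that falls during testing or exercise and temporary symptom aggravation are foreseeable. No new pain item is needed.

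**Cost:** one question at four existing visits, one field on the training sheet and a short amendment.

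**Downsides:** slightly longer visits, a less reassuring harms statement, and data that stay descriptive at 33 per arm. The question equalises the opportunity to report but not recall: a fall already discussed at training may be better remembered at the visit, and the interval from week 6 to week 12 is the longest to recall in both arms.

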### Data management

The researchers shall fill in data to the data collection sheet accurately, completely, and timely based on original observations. MH will be responsible to fill in data collection sheets during each evaluation, and CT will be responsible to fill in data collection sheets during each intervention. Researchers are responsible for ensuring the accuracy of all data entered and recorded. All data collected during this study are totally confidential and will never allow participant identification. Confidentiality will be assured by replacing the participants’ names by an alphanumeric code. The data collected will be stored under lock and key in the evaluation or intervention room (paper documents) or on a secure network with both network and electronic document access protected by passwords under the responsibility of the Chaire de recherche internationale en santé neuromusculosquelettique at the Université du Québec à Trois-Rivières. Only the research members will have access to these data. All of them have signed a confidentiality agreement. All data will be destroyed 5 years after the end of the study. For monitoring and control purposes, research files may be consulted by a person mandated by the CIUSSS MCQ Research Ethics Board or by a person mandated by authorized public agencies. All these persons and organizations adhere to a confidentiality policy. Full name, contact information, and the start and end date of participation for each participant in the project will be kept for 1 year after the end of the project in a separate directory maintained by the researcher responsible (MH) for this research project. For randomization purposes, a research assistant will have access to baseline data. This research assistant has also signed a confidentiality agreement.

### Plans to give access to the full protocol, participant-level data

Detailed information on the study including study design, eligibility criteria, and outcome measures is currently available to the public on clinical trials. Datasets analyzed during the study, statistical code, and materials are available from the corresponding author upon reasonable request.

### Composition of the coordinating center and trial steering committee and plans for auditing trial conduct

The coordinator of the study is MH. She is responsible for all aspects of the local organization including identifying potential recruits and taking consent from participants. In addition to MH, CEC is responsible for the identification of potential recruits in the regional hospital outpatient clinic. CT (certified kinesiologist) is the supervisor of each session of exercises for the intervention group. The project is supervised by MD and AAM. Both are professors at UQTR and are supervising MH’s doctoral studies. The local Trial Steering Committee is composed of MH, CT, CEC, AAM, and MD. The team discussed the test protocols, the intervention content, and the related materials together. The committee will meet each month throughout the study. If there is any modification to the protocol that needs to be done or if there is any adverse event, the TSC will discuss the situation as soon as possible and will inform the research ethic committee. The monitoring will be conducted by the principal investigator of the study each month as an audit of trial conduct. There is no stakeholder and public involvement group for this study.

### Dissemination plans

The results will be communicated to participants, healthcare professionals, the public, and other relevant groups via publications in scientific journals, platform presentations, and poster presentations during national and international congresses.

## Discussion

The interventions for this RCT were designed according to the best available treatment guidelines and best practice recommendations which include the use of education and an individually tailored supervised exercise program [17, 38]. A recent systematic review focusing on multidisciplinary interventions for chronic pain reported that education should be incorporated into future RCTs because of its contribution to the improvement of chronic pain management especially with regard to self-efficacy. This improvement was observed when education was used as either the active or the control intervention [39]. In addition, a previous qualitative study reported that short bouts of education about exercise techniques improved symptoms related to LSS causing NC [40]. According to Backstrom and colleagues, education should include information related to LSS such as its definition, symptoms manifestations, the natural course of the condition, the purpose of home exercises, information related to pathophysiology, and self-management strategies [41]. Self-management strategies are essential in the management of persistent musculoskeletal conditions such as LSS and should be an important part of education programs [42]. Recently, patient education under many forms (e.g., pathoanatomical descriptions, etiologies, self-management strategies, nutrition modifications, and physical activity) has been included in RCTs for LSS [20, 22, 43, 44]. However, there was heterogeneity regarding education content, intervention duration, and outcome measures among the studies making it difficult to draw conclusions on the best parameters of education to be used. Building on previous findings, the present protocol study will provide a standardized education program for both groups. This should help patients better understand their condition and why exercises can be used to improve walking capacity. In addition, the use of a standardized education program will allow us to isolate the effect of the exercises on the improvement of walking capacity in patients with LSS causing NC.

Regarding rehabilitation programs, the effectiveness of exercises alone in improving objective walking capacity is still not well established [17]. A recent systematic review reported low to moderate-quality evidence for multimodal programs including exercises on the improvement of symptoms and function in patients with LSS causing NC [45]. In addition, another previous RCT showed that the use of supervised exercises provided significantly greater improvement in walking distance, physical function, and symptoms severity compared to self-directed exercises [46]. Similarly, another RCT of Comer et al. showed that a self-directed home exercise program including flexion and aerobic exercises punctually prescribed by physiotherapists did not systematically improve symptom severity and was no more effective than education and advice [22]. However, in most previous RCTs, exercise intensity was not tailored to day-to-day symptom severity. Thus, the present protocol is innovative in two respects: it includes standardized education for all participants, and it takes into consideration the day-to-day evolution of symptom severity to provide a tailored exercise program.

Previously reported rehabilitation programs usually included aerobic and lower limb-strengthening exercises [20, 47–50] but did not incorporate balance-strengthening exercises. However, patients with LSS and NC present an increased risk of falls for a variety of reasons, including deconditioning, lower extremity neurological deficits, polypharmacy, environmental hazards, poor vision, and impairments in gait and activities of daily living [51]. In addition, a previous study by Thornes et al. showed that there was a large inter-individual variation in balance between patients with LSS and NC and that gait stability was negatively associated with disability as measured by the ODI [52]. Based on those findings and knowing that balance limitations have been identified in 45 to 65% of patients with LSS [53, 54], the present protocol will include balance exercises to help decrease the risk of falls in patients with LSS causing NC and to contribute to patient’s self-confidence during walking.

Another point to consider when assessing the effectiveness of any intervention is the primary outcome measure. To date, most studies using exercises as the main intervention for LSS used indirect measures of walking capacity such as functional capacity measured by the SSSQ or the Zurich Claudication Questionnaire (ZCQ), leg and back pain intensity, disability measured by the ODI or the global rating of change scale as their primary outcome [46, 48–50]. Considering that a decrease in walking capacity is considered one of the most bothersome consequences of LSS causing NC [12], direct measures of walking capacity using a self-paced walking test should be used when assessing the effectiveness of interventions on functional capacities.

Overall, having a flexible rehabilitation program combining lower limb strengthening and balance exercises should lead to an improvement in walking capacity for patients with LSS causing NC. In addition, it should increase self-efficacy and decrease anxiety. This will also provide patients with a conservative treatment option that takes into consideration the day-to-day fluctuation in symptom severity. To our knowledge, this is the first LSS-specific rehabilitation program providing standardized education and graded exercises aimed at improving walking capacity regardless of patients’ current healthcare trajectories.

This study protocol also presents innovative components. Indeed, by adding inertial wearable sensors during the SPWT walking evaluation, this study will provide original and accurate information about the gait pattern characteristics of patients with LSS causing NC. By monitoring the gait biomechanical parameters throughout the study, we will also be able to determine which ones are modified by exercises and how they are modified. This could eventually help researchers and clinicians better understand the patient’s biomechanical adaptations over time as well as the impact of specific exercises on walking capacity or gait pattern characteristics. Findings from this study may eventually lead to improvement in the evaluation and management of patients with LSS causing NC.

## Data Availability

Original consent form, data, and materials are available upon reasonable request to the authors.
